***Other secondary outcome measures***

Other secondary outcome measures are:Mental health and general psychiatric symptoms as measured with the ***Brief Symptom Inventory (BSI)*** [62] and the ***Outcome Questionnaire-45 (OQ-45)*** [63].General happiness as measured with the ***happiness item*** [64].Health care costs and lost productivity costs as measured with the ***Trimbos/iMTA questionnaire and Costs associated with Psychiatric illness (TiC-P)*** [65].Quality of life as measured with the ***EuroQol 5D (EQ-5D-5 L)*** [66].

#### Moderators and mechanisms of change

##### General patient characteristics

General patient characteristics will be collected at baseline, such as treatment history, DSM-IV/5 diagnoses, medication use, age, gender, marital status and educational level.

##### Treatment condition

The treatment condition, being either SPSP or ST will be reported in order to measure whether the effect of frequency is moderated by the type of therapy.

##### Level of discourse in SPSP

The dominant level of discourse will be reported by the SPSP-therapist at 1, 2, 3, 6 months and at end of treatment, ranging from level one focusing on physical and psychological symptoms to level eight focusing on the manifestation of the problems in the patient-therapist relation. This therapist-report scale will be developed for the study.

##### Dominant schema mode

The dominant schema mode active during the sessions will be reported by the ST-therapists at 1, 2, 3, 6 months and at end of treatment. Twelve dysfunctional and two functional modes can be selected. This therapist-report scale will be developed for the study.

##### Working alliance: working alliance inventory-short form [67, 68]

The WAI-sf intends to measure components of the therapeutic alliance by investigating the tasks, bonds and goals therapist and patient have. Behaviors and cognitions that form the therapeutic process, positive personal attachments between patient and therapist, and having set mutually endorsing and valuing goals are part of these components. The questionnaire consists of 12 items rated on a 5-point Likert scale and will be filled out by both patient and therapist. The instrument has shown adequate psychometric properties. It will be administered monthly in the first 3 months, at 6 months and at the end of therapy.

##### Therapist’s adherence

All sessions will be audio-taped and a planned selection of three sessions per patient (6–12%) will be scored by independent raters in order to measure therapists’ adherence to the treatment condition. For schema therapy an unpublished treatment integrity scale is used, developed for previous research [16]. Because no adherence scale for SPSP has been developed yet, this will be developed by SPSP-supervisors.

### Ethical and safety reporting

Serious adverse events (SAE; e.g. life-threatening events, resulting in permanent damage or death) will be documented throughout the study. In case of an SAE the principal investigator will be informed and will report the SAE to the local ethics committee. The ethics committee and the study team will then decide in accordance with the best interest of the patient if the study procedures are continued or terminated.

### Data handling and storage

At inclusion, a unique number will be allocated to each subject. The key of these numbers will only be available to the corresponding author and two data analysts who conduct randomization. All data will be stored encoded and in password protected files. Storage of data will be supervised by the principal investigator and complies with the Dutch Personal Data Protection Act (“WBP”).

### Data analyses

#### Clinical outcome: depression

Data-analysis will include an intention-to-treat analysis. Baseline characteristics and antidepressants used during treatment will be examined in the two dosage conditions (25 and 50 sessions) and potential confounding factors will be added as covariates in the analyses.

The primary outcome measure is depression severity (BDI-II). Relative effectiveness of the two dosage conditions (25- vs 50-sessions) will be analyzed using linear mixed models, with the underlying distributional model based on the distribution of the dependent variable and the residuals (e.g. normal, gamma, negative binomial). With this model missing values can be dealt with effectively. This analysis will be conducted according to a four-level structure (patient, therapist, location and time). The growth curve on depression severity over time can be shown with this model. The proportion of patients that achieve reliable and clinically significant improvement at termination and follow-up will be calculated on the outcome measure (BDI-II) for both dosage conditions, and secondary for both therapy-conditions (ST/SPSP). These calculations will be based on the reliable change index [69]. Comparison between the dosage conditions (and secondary between the therapy-conditions) will be analyzed with generalized estimating equations (GEE). In addition, remission rates will be measured and compared for the dosage conditions (and secondary for the therapy-conditions) at termination and follow-up (MINI-plus, section A and B) using GEE. In exploratory analyses, the interaction of treatment condition and dosage condition will be analyzed for all outcome measures.

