### Participants

The study is conducted at the NPI, specialist in PD on two locations in Amsterdam (North and East). General criteria for referral are either insufficient results of earlier psychiatric or psychologic treatment or recurrence of depressive symptoms, clinically attributed to PD.

We aim to include 200 patients who meet the following criteria: 1) a DSM-5 depressive disorder (major depressive disorder or persistent depressive disorder) *and* one or more DSM-5 personality disorders, and 2) age 18–65 years. Patients will be excluded in case they: 1) are non-Dutch speakers/readers, 2) have psychotic symptoms, a bipolar disorder or current extreme substance dependence, 3) are in need of immediate and intensive treatment or hospitalization, e.g. acute suicidality according to the intake clinician, 4) are pregnant or unavailable for an uninterrupted period of more than 4 weeks 5) use medication which highly influences mental functioning according to a psychiatrist. No additional psychotherapy can be provided when participating in the trial, as this would exceed the assigned psychotherapy dosage. However, a psychiatrist can be consulted and pharmacotherapy can be provided if indicated. The consultation of psychiatrists and the prescribed pharmacotherapy during the trial will be monitored on the basis of information from the electronic prescription system as presented in Table 1. The Mini International Neuropsychiatric Interview-plus (MINI-plus) section A (Depression) and B (Dysthymia) will be used to diagnose depressive disorders until a version of the MINI-plus is available for DSM-5. The SCID-screener (SCID-PQ / SCID-5-SPQ) followed by the Structured Clinical Interview for DSM-IV personality disorders (SCID-II) or when available DSM-5 (SCID-5-PD) will be used to determine personality disorders.

**Table 1 Tab1:** Monitoring of the pharmacotherapy delivered during the trial

Medication type	Dosage	Start date	End date
Antidepressants	ᅟ		
Benzodiazepinen			
Antipsychotics			
Other medication			

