### Randomization and procedure

An independent research assistant will contact eligible patients within a week after intake and will invite the patient for research assessment. Additional information about the study is provided by email, giving the patient the time to consider participation. During the assessment meeting any doubts or questions about participating in the study can be discussed with the research assistant. The MINI-plus (section A and B) and the BDI-II will be assessed during research assessment and if no structured diagnostic interview has been completed during intake, the SCID-II / SCID-5-PD will be conducted. If the patient is eligible and willing to participate an informed consent is signed. Patients will then be randomized by one of two research department employees in one of four groups (with a 1:1:1:1 allocation) using a computer script performing block randomization (25 vs 50-sessions; ST vs SPSP). Randomization will be pre-stratified according to depression severity (BDI-II < =29 low, BDI-II= > 30 high). Treatment starts as soon as possible (approximately within 0 to 3 months) and patients are assigned to a therapist based on the allocated condition and the therapists availability. Patients will be assigned for the online baseline assessment in the week prior to the start of therapy. During the course of treatment patients will be requested to fill in short online assessments at 1, 2 and 3 months. At 6 months, end of treatment and follow-up extra questionnaires are added. The data collection process is monitored in detail and patients who don’t fill out the questionnaires will be reminded by the research assistant. In addition to the online measurements the SCID-II / SCID-5-PD and MINI-plus (section A and B) will be assessed at treatment termination (9–12 months) and follow-up (21–24 months) by a research assistant who is blind for condition. All data collected from interviews during research assessment at baseline, end of treatment and follow up will be entered and stored on site. Online submitted data forms are converted to the onsite database by the data analyst. All online submitted data will be checked by a research assistant on missing data or specific errors. Independent random data checks will be conducted on entry and encoding errors. All data is entered electronically. As part of the analysis, standard checks on double data entry and range checks on data values will be performed.

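### Antidepressant use during treatment is a candidate covariate for the dosage comparison, although it arises after randomisation and cannot confound a randomised effect

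*Protocol article*

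**What the plan says.** The section Clinical outcome: depression opens with the principle "Data-analysis will include an intention-to-treat analysis". The next sentence sets the covariate rule: "Baseline characteristics and antidepressants used during treatment will be examined in the two dosage conditions (25 and 50 sessions) and potential confounding factors", continuing that "potential confounding factors will be added as covariates in the analyses". BDI-II severity is then named as the primary outcome, to be analysed with linear mixed models. The article gives no list of covariates and no criterion for what counts as a confounder. It does not restrict covariates to values from before randomisation, and it does not describe the antidepressant adjustment as a sensitivity analysis.

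Four other places bear on the point:

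- **Participants** bars additional psychotherapy during the trial but adds: "However, a psychiatrist can be consulted and pharmacotherapy can be provided if indicated". It also says that "The consultation of psychiatrists and the prescribed pharmacotherapy during the trial will be monitored", with start and end dates in Table 1.
- **General patient characteristics** lists, among the variables collected at baseline, "medication use, age, gender, marital status and educational level".
- **Randomization and procedure** states: "Randomization will be pre-stratified according to depression severity". The BDI-II used for this is taken at the research assessment, before allocation.
- **Economic evaluation** counts medication among the costs to be compared between the two dosage conditions.

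**The concern.** A confounder of the dosage effect would have to influence which dosage a patient receives. Dosage is assigned at random, so nothing that happens afterwards can do that. Antidepressant use during treatment can instead play two other roles:

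- **Intermediate.** Medication is an open route for a patient who is not improving, and improvement is what 50 sessions are hypothesised to increase. Holding use constant then takes out, or adds back, whatever part of the effect runs through prescribing.
- **Collider.** Use may depend on dosage and also on unmeasured prognosis. Comparing users with users and non-users with non-users across arms then compares patients of different prognosis, and the protection of randomisation is lost.

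The article's two uses of medication also sit badly together. The economic evaluation treats it as something dosage may change; the covariate rule treats it as something that may confound dosage. At stake is the trial's main comparison, which the same section promises to analyse by intention to treat.

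**Working it through.** **Yardstick.** The sample size section plans for d = 0.45, two-sided α = 0.05 and power 0.80. Per dosage group, n = 2 × (1.960 + 0.842)² / 0.45² = 77.5, that is 78, as stated. The effect of 0.45 SD serves below only as a scale.

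**Formula.** Let D be the benefit of 50 over 25 sessions in SD of BDI-II, p25 and p50 the proportions using antidepressants during treatment, and b the within-arm difference in BDI-II between users and non-users (positive if users are more depressed). In a linear model:

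adjusted D = D − b × (p25 − p50)

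The shift is zero when p25 = p50. Its sign depends on the signs of both b and p25 − p50.

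**Inputs.** The article gives no rate of use, arm difference or association with BDI-II, so all of these are assumptions: p25 = 40%; p50 = 40%, 30% or 20%; and a correlation ρ of 0.3 or 0.6 between the underlying tendency to use and unmeasured prognosis. If the drug itself has no effect on BDI-II, the normal threshold model gives

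b = ρ × [φ(z25) + φ(z50)] / [p25(1 − p25) + p50(1 − p50)]

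where φ is the normal density at the threshold: 0.386 for 40%, 0.348 for 30% and 0.280 for 20%.

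- p50 = 30%: b = ρ × (0.386 + 0.348) / (0.24 + 0.21) = 1.63ρ
- p50 = 20%: b = ρ × (0.386 + 0.280) / (0.24 + 0.16) = 1.67ρ

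| p50 | ρ | b | shift = b × (p25 − p50) | 0.45 becomes |
|---|---|---|---|---|
| 40% | either | – | 0 | 0.45 |
| 30% | 0.3 | 0.49 | 0.05 | 0.40 |
| 30% | 0.6 | 0.98 | 0.10 | 0.35 |
| 20% | 0.3 | 0.50 | 0.10 | 0.35 |
| 20% | 0.6 | 1.00 | 0.20 | 0.25 |

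A simulation with two million patients per scenario returns the same values. With a true effect of zero, the four unequal-use scenarios give an adjusted estimate 0.05 to 0.20 SD against 50 sessions.

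**Opposite direction.** Suppose use is unrelated to prognosis and the drug lowers BDI-II by 0.3 SD, so b = −0.3. The adjusted benefit is then too large by 0.3 × 0.10 = 0.03 SD (p50 = 30%) or 0.3 × 0.20 = 0.06 SD (p50 = 20%). By the same formula, the sign also reverses if use is higher in the 50-session arm.

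**Without the adjustment.** In every scenario the model without on-treatment use recovers the full dosage effect.

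**The case against.** The strongest reply is that the article does not commit to the adjustment. It says that variables are examined in the two conditions and that potential confounders are added. No test, threshold or imbalance trigger is written, and an analysis plan that is not shown may define one, or may leave antidepressants out. This stands in part: inclusion is possible, not certain. A reader might infer that a difference between arms automatically brings the variable in. That is a natural reading of examining it by arm, but it is not stated. What remains is that the published rule names a post-randomisation variable as a candidate confounder, and nothing else in the article withdraws it. This is a stated rule, not a detail left out.

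Second, some use during treatment continues from before randomisation. The Discussion says that nearly all patients have had earlier treatment, some of it with antidepressants. Continued use need not be a response to dosage. That is fair, and it favours adjusting for use at baseline, not for use during treatment.

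Third, a reader might infer that adjustment always dilutes the dosage effect. The working shows that it need not.

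Fourth, a reader might conclude that the primary model omits the BDI-II stratum, baseline BDI-II and therapy type, and so loses power. The document does not support this. A journal article commonly leaves full model terms to the protocol or analysis plan. The planned analysis is a longitudinal mixed model with BDI-II measured before and repeatedly during therapy, not a comparison of end scores alone.

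**Conclusion.** The concern holds in a limited form. The covariate rule admits on-treatment antidepressant use as a possible adjustment in the dosage comparison, and that variable cannot be a confounder of a randomised effect. If it is included and dosage has changed its use, the estimate is no longer the intention-to-treat effect of dosage.

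The shift is 0 if dosage does not change use. In the scenarios above it reaches about 0.2 SD, which is 0.20 / 0.45 = 44% of the planned effect. That upper figure needs use to halve from 40% to 20% and a correlation of 0.6 with prognosis, neither of which comes from the document. The figures illustrate the mechanism and do not predict this trial's bias, whose direction is also open.

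Because inclusion is conditional and the harm may be nil, this is something that should be corrected, not a flaw that invalidates the plan.

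**What to change.** State that the primary dosage analysis is not adjusted for antidepressant use during treatment. Report that use by arm, from the monitoring already planned. If its role is of interest, examine it in an analysis labelled as supplementary or as mediation.

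Replace the examination of candidates by arm with a set of pre-randomisation covariates fixed before the arms are compared. Suitable members are BDI-II from the research assessment or its stratum, therapy type and, if wanted, antidepressant use at baseline. The online baseline assessment takes place after allocation, in the week before therapy starts, so the text should say that covariate values are those from before randomisation.

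The cost is a change of wording. The BDI-II at assessment, its stratum and therapy type are already recorded, and medication use is already collected at baseline, though its date relative to randomisation needs to be confirmed. The small downside is that a chance imbalance in another baseline variable is handled in a sensitivity analysis and not in the primary model. The article reports recruitment as ongoing, so the change can be made before outcomes are compared by arm.

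### The covariate rule for the depression analyses admits antidepressant use during therapy, a post-randomisation variable; adjusting for it can move the 25 v 50 estimate away from the total dosage effect in either direction

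*Protocol article*

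**What the plan says.** The Data analyses section, under Clinical outcome: depression, opens with "Data-analysis will include an intention-to-treat analysis". The next sentence sets the covariate rule. Together with baseline characteristics, "antidepressants used during treatment will be examined in the two dosage conditions (25 and 50 sessions) and potential confounding factors will be added as covariates". The primary model follows directly: "Relative effectiveness of the two dosage conditions (25- vs 50-sessions) will be analyzed using linear mixed models". The rule is not confined to a sensitivity or mediation analysis, and covariates are not limited to pre-randomisation variables.

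Two other places matter. Under Participants, during the trial "a psychiatrist can be consulted and pharmacotherapy can be provided if indicated", and "the prescribed pharmacotherapy during the trial will be monitored on the basis of information from the electronic prescription system"; Table 1 there records start and end dates. Under General patient characteristics, medication use is also gathered at the outset: "General patient characteristics will be collected at baseline, such as treatment history, DSM-IV/5 diagnoses, medication use, age, gender".

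**The concern.** A confounder of the dosage comparison would have to influence which dosage a patient receives. Dosage is allocated by randomisation, so nothing that happens afterwards can do that. Antidepressant use during therapy may respond to how the patient is doing, because pharmacotherapy is given on indication. The primary hypothesis is that dosage changes how the patient is doing. A link from dosage to prescribing is therefore plausible, though not shown.

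If the link exists, the variable is a mediator, a marker of poor course, or both. Conditioning on it changes the question from what 50 rather than 25 sessions does to depression, to what it does at a given level of drug use. That second quantity is also open to bias from whatever drives both prescribing and BDI-II. At stake is the primary comparison: an estimate that partly reflects prescribing patterns, with altered power or type I error.

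**Working it through.** **The plan's own figure.** From Sample size: d = 0.45, two-sided α = 0.05, power 0.80. The normal approximation gives n = 2 × (1.960 + 0.842)² / 0.45² = 2 × 7.85 / 0.2025 ≈ 77.5, so 78 per dosage group, as stated. After the stated 25% dropout, 200 × 0.75 = 150 remain, or 75 per group; the second check uses that number.

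**How the shift arises.** In a linear model with arm and antidepressant use only, 

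adjusted effect = total effect − γ × (p50 − p25),

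where p50 and p25 are the proportions using antidepressants in each arm and γ is the coefficient of use in the adjusted model. The sign of the shift depends on the sign of γ and on which arm uses more. The shift is zero when p50 = p25.

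**Check 1: large-sample simulation, no baseline covariate.** All prescribing inputs are assumptions. A negative value favours 50 sessions.

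| Scenario | Use, 25 v 50 | γ | Total | Adjusted |
|---|---|---|---|---|
| Drug effect only | 50% v 31% | −0.30 | −0.45 | −0.51 |
| Drug effect only | 50% v 69% | −0.30 | −0.45 | −0.40 |
| Marker of poor course, no drug effect | 50% v 34% | +0.55 | −0.45 | −0.36 |
| Marker of poor course, no drug effect | 50% v 66% | +0.56 | −0.45 | −0.54 |
| Marker plus drug effect | 50% v 34% | +0.26 | −0.45 | −0.41 |
| Marker, no dosage effect | 50% v 34% | +0.56 | 0 | +0.09 |
| Marker, no dosage effect | 50% v 66% | +0.56 | 0 | −0.09 |
| Dosage does not change use | 50% v 50% | +0.25 | −0.45 | −0.45 |

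Worked example (third row): −0.452 − 0.554 × (0.341 − 0.501) = −0.452 + 0.089 = −0.363.

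**Check 2: 75 per arm, baseline severity in the model.** Again all assumed:
- Baseline b ~ N(0, 1).
- Mid-therapy severity = 0.6b + noise (SD 0.8) − half the dosage effect.
- P(antidepressant) = Φ(Φ⁻¹(0.3) + 1.0 × mid + δ × arm).
- End severity = 0.6 × mid + noise (SD 0.8) − remaining dosage effect − drug effect × use.

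The outcome was regressed on arm and b, with and without use, over 8,000 replicates. Effects are benefits of 50 sessions in SD. The drug effect is 0.3 where dosage has an effect and 0 in the null rows.

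| Scenario | Use, 25 v 50 | Without use | With use | Rejection rate, without → with |
|---|---|---|---|---|
| d = .45, δ = −0.5 | 36% v 19% | 0.40 | about 0.365 | 75–76% → 66% |
| d = .45, δ = 0 (use differs through severity only) | 36% v 30% | 0.43 | 0.42 | 82% → 80% |
| d = .45, δ = −0.5, use unrelated to severity | 30% v 15% | 0.41 | 0.45 | 75% → 82% |
| d = .45, δ = −0.5, 40% already using | 61% v 51% | 0.42 | 0.43 | 78% → 79% |
| No effect, δ = −0.5 | 36% v 23% | 0 | −0.06 | 5% → 7% |
| No effect, δ = +0.5 | 36% v 49% | 0 | 0.07 | 5% → 7% |
| No effect, δ = +1.0 (extreme) | 36% v 63% | 0 | 0.14 | 5% → 13–14% |
| No effect, δ = 0 | 36% v 36% | 0 | 0 | 5% → 5% |

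These scenarios illustrate; they do not bound. For example, setting the drug effect to zero in the first row moves 0.45 to 0.36 and power from 83% to 66%.

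**The case against.** The strongest reply has four parts.

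1. **Adjustment is allowed, not prescribed.** The variables are to be examined and potential confounders added, and no criterion is given. This stands: the text does not make adjustment certain. But the only screen described is an examination across the dosage arms, and no imbalance in a post-randomisation variable can make it a confounder.

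2. **Intention to treat is not contradicted.** A reader might infer a contradiction between the two adjoining sentences. The documents do not support that. The article says an intention-to-treat analysis will be included, and a covariate leaves patients in their allocated arm. What changes is the quantity estimated.

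3. **An effect of dosage on prescribing is not shown.** This also stands. The article says only that pharmacotherapy may be given on indication. The Discussion notes that almost all patients have been treated before, some with antidepressants, so part of the in-trial use may simply continue earlier use. With an assumed 40% carried over, the shift nearly vanishes and type I error stays near 5%.

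4. **The direction is not fixed.** A reader might infer that more prescribing in the 25-session arm must hide part of a real benefit. That is not general: where use is unrelated to severity, adjustment raises the estimate from about 0.40 to 0.45.

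A reader might also quote larger figures from the second simulation: effect 0.40 to 0.33, power about 72% to 55%, type I error 22% in the extreme case. Those arise only when baseline severity is left out. BDI-II is measured at the start of therapy, randomisation is stratified by it and the planned model is longitudinal, so the smaller figures are the fairer guide.

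That the analysis plan is not shown does not answer the point. The article names this variable as a candidate covariate, so this is a rule stated badly rather than a detail left out.

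**Conclusion.** The point holds in limited form. The rule allows a post-randomisation variable into the depression analyses on the ground of confounding, which it cannot cause in a randomised comparison. If it is added and dosage affects prescribing, the coefficient no longer estimates the total dosage effect, and the direction of the shift cannot be known in advance.

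In the tabulated scenarios with baseline severity in the model, the shift is about 0.01 to 0.07 SD (0.14 SD in the extreme case) against a planned effect of 0.45 SD. Power changes by up to about 10 points either way. Type I error is about 7%, and up to 14% in the extreme case. Other assumptions can give somewhat more, as the zero-drug-effect example shows. If dosage does not change prescribing there is essentially no shift. Every prescribing rate, drug effect and severity link is assumed, because the article gives none. The conclusion about what is being estimated does not rest on these figures.

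**What to change.** Amend the covariate sentence so that the primary 25 v 50 model uses only prespecified pre-randomisation variables, for example baseline BDI-II or its randomisation stratum, and baseline medication use, which the article already collects. One precision is worth adding. Randomisation follows the assessment meeting, and therapy may start up to about three months later, so covariate values should be taken as of randomisation rather than at the start of therapy.

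Report in-trial antidepressant use descriptively by arm from the monitoring data. If an effect under equal medication is wanted, label it as a secondary or sensitivity analysis and use a method suited to post-randomisation variables, such as inverse-probability weighting or a mediation analysis with its assumptions stated.

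The cost is one sentence in the protocol or the analysis plan, plus a check that medication status at randomisation can be retrieved. No extra patients or visits are needed, and the article reports that recruitment is still under way.

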### Sample size

We powered the study to detect a difference of d = .45 between groups for depressive symptoms (BDI-II) [29] given the meta-analysis of session frequency in depressed patients described above, which reported an effect size of 0.45 when treatment sessions were given twice rather than once a week [29].According to this effect size (and given our choices of α = 0.05, two-tailed, power (1-β) = 0.80) 78 patients are needed in both dosage-groups. When 25% dropout is taken into account at least 200 patients will be needed for inclusion. With this sample size differences between SPSP and ST can be detected (with ≥80% certainty) if they differ at least d = .45.

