The analyses will be done according to the intention-to-treat principle. Missing cost and effect data will be imputed using multiple imputation. Incremental cost-effectiveness-ratios (ICERs) will be calculated by dividing the difference in the mean total costs between the treatment groups by the difference in mean effects between the treatment groups. Uncertainty around the ICER will be calculated using a non-parametric bootstrap approach. For each of these bootstrapped samples, the incremental costs, incremental effects, and the ICER will be calculated. The resulting ICERs will be used for further calculations and will be plotted on a cost-effectiveness plane. In addition, cost-effectiveness acceptability curves (CEACs) will be constructed to show the probability that the 50-sessions intervention is cost-effective compared to the 25-sessions intervention, as a function of willingness-to-pay per additional unit of effect (QALYs or BDI symptoms). One-way sensitivity analyses directed at uncertainty in the main cost drivers will be performed to gauge the robustness of our findings.

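### The GEE comparisons of remission and reliable change have no stated missing-data handling, and standard GEE would not use the earlier BDI-II scores that may predict missed interviews

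*Protocol article*

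**What the plan says.** Under Data analyses, the subsection on depression assigns a linear mixed model to BDI-II severity and adds "With this model missing values can be dealt with effectively". That sentence refers to the mixed model only. The same subsection assigns GEE to BDI-II reliable and clinically significant change, and to MINI-plus remission: "In addition, remission rates will be measured and compared for the dosage conditions (and secondary for the therapy-conditions) at termination and follow-up". The subsection on personality parameters assigns GEE to reliable change on personality measures and to SCID remission. Neither subsection says how missing values are handled in these GEE analyses. The clinical analysis is described as intention-to-treat.

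In the Economic evaluation section, "Missing cost and effect data will be imputed using multiple imputation". The effect measures there are the BDI-II and EQ-5D-based QALYs; MINI-plus and SCID diagnoses are not among them.

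The Sample size section states "When 25% dropout is taken into account at least 200 patients will be needed for inclusion". Table 2 schedules the MINI-plus after baseline only at the end of therapy and at 12-month follow-up. The BDI-II is also scheduled at months 1, 2, 3 and 6 and at 6-month follow-up. Under Randomization and procedure, patients who stop treatment early are asked to complete all remaining assessments.

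**The concern.** A likelihood-based mixed model and standard multiple imputation both allow missingness that depends on earlier observed scores. Standard unweighted GEE does not, unless those scores are covariates in its model. Here the scores that may predict a missed interview are the month 1 to 6 BDI-II values, which the trial collects anyway. They cannot simply be added as GEE covariates: they are measured after randomization and lie between dosage and outcome, so adjusting for them would distort the dosage effect. They belong in an imputation or weighting model.

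A patient who misses both MINI-plus interviews contributes nothing to an available-case GEE of remission, which fits poorly with the intention-to-treat statement. The matter carries weight because the abstract lists remission with depression severity as the primary clinical outcome, and the primary hypothesis under Objective includes higher remission rates. The article also expects dropout in such samples to be relatively high and plans to compare treatment dropout between conditions.

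**Working it through.** **1. The plan's own figure.** From Sample size: d = 0.45, two-sided alpha 0.05, power 0.80. Per group, n = 2 × (1.960 + 0.842)² / 0.45² = 2 × 7.849 / 0.2025 = 77.5, so 78. This reproduces "78 patients are needed in both dosage-groups". It concerns BDI-II severity; no figure is given for remission. If the full 25% were missing outcomes, 200 × 0.75 = 150 patients would remain, 75 of 100 per dosage arm.

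**2. What GEE returns.** In simulated data where dropouts miss both interviews, a logistic GEE (arm, time, arm × time, exchangeable working correlation) gave end-of-treatment rates of 43.6% and 60.7%. These equal the observed proportions, so it makes no correction for who left.

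**3. Source of bias.** Let x be earlier severity, π(x) the probability of a missing outcome and R remission. The observed rate in an arm is

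E[(1 − π(x)) × P(R = 1 | x)] / E[1 − π(x)].

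This equals the true rate if π is constant or x is unrelated to R. The error in the dosage difference is the error in the 50-session arm minus that in the 25-session arm.

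**4. Illustration A.** All inputs are assumed: true remission 40% vs 55% (difference 15 points), correlation 0.6 between earlier severity and outcome, logistic dropout with slope 1 on earlier severity where it depends on it, 400,000 patients per scenario.

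| Dropout depends on severity | Dropout, 25 / 50 sessions | Observed rates, 25 / 50 sessions (%) | Difference (points) |
|---|---|---|---|
| In neither arm | 25% / 25% | 40.0 / 54.9 | 14.9 |
| Equally in both arms | 25% / 25% | 44.8 / 60.0 | 15.2 |
| Equally in both arms | 30% / 20% | 45.7 / 59.3 | 13.6 |
| Equally in both arms | 20% / 30% | 43.8 / 61.1 | 17.3 |
| In the 25-session arm only | 25% / 25% | 44.5 / 55.1 | 10.6 |
| In the 50-session arm only | 25% / 25% | 39.8 / 60.2 | 20.4 |
| In opposite directions | 25% / 25% | 44.6 / 50.0 | 5.3 |

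A model-based estimate using the earlier score, standing in for multiple imputation, stayed at 15.0 to 15.4 throughout. Numerical integration of the formula in step 3 agrees with the differences in the table to within half a point.

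**5. Illustration B.** Different assumed inputs: true remission 35.0% vs 52.5% (difference 17.5), correlation 0.7, about 25% dropout, 1,000,000 patients per arm.
- Slope 1 in the 25-session arm only (dropout 26.9% / 24.9%): 40.7% vs 52.5%, difference 11.9, an error of 11.9 − 17.5 = −5.6 points.
- The reverse: difference 23.2, an error of 23.2 − 17.5 = +5.7 points.
- Slope 0.8 in both arms: 39.6% vs 57.0% against simulated true rates of 35.0% and 52.6%, difference 17.4.

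**6. Reading the two together.** With dependence in one arm only, the error is about 4 to 6 points in either direction. With a common mechanism and equal dropout the difference is nearly right, but the arm rates are too high: 44.8 − 40.0 = 4.8 and 60.0 − 54.9 = 5.1 points in A. The common mechanism in B gives 39.6 − 35.0 = 4.6 and 57.0 − 52.6 = 4.4. A common mechanism with 20% vs 30% dropout shifts the difference by about 2 points.

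**The case against.** The strongest reply is that the article names an estimator and stops. It nowhere says the GEE will be unweighted or restricted to observed cases, and GEE can be combined with imputation or weighting. The full protocol or analysis plan may add this. That stands: a reader might infer that the plan has chosen an observed-case analysis, but the document does not say so. What remains is that the article does discuss missing data for clinical outcomes, confines that statement to the mixed model, and limits imputation to the economic evaluation. Applied as written, GEE would use the available interviews.

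Other parts of the reply also stand.
- To say GEE needs data missing completely at random would be too strict. Missingness that depends on model covariates is allowed, and the plan foresees covariates such as baseline characteristics and antidepressant use. Earlier post-baseline BDI-II scores are not among those named.
- The 25% need not be the share of missing remission outcomes. It is a planning figure for dropout, while patients who stop treatment are asked to continue assessments and non-responders are reminded.
- One might read the plan as making three different missing-data assumptions. It uses three methods, but the mixed model and standard multiple imputation share one assumption; only GEE is stricter.
- The analysis section names BDI-II severity as the primary outcome measure, and the power calculation rests on it. The main mixed-model analysis is not affected.
- Nothing in the document shows that dropout mechanisms will differ by arm. Different session frequencies make it plausible, no more.

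**Conclusion.** The point holds in a limited form. The plan assigns GEE to MINI-plus remission, BDI-II reliable change and SCID remission without extending any missing-data handling to them, and standard GEE would ignore the month 1 to 6 BDI-II scores. The remission difference is biased if outcome dropout depends on those scores differently in the two dosage arms: illustratively by about 4 to 6 points, in either direction, when severity drives dropout in one arm only. With equal dropout and a common mechanism the difference is nearly unbiased, and only the arm-specific rates suffer, by about 4 to 5 points.

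These sizes rest on assumed remission rates, correlations and dropout slopes, and on about 25% missing outcomes; fewer missing outcomes would generally mean less bias. The document does not support concluding that the remission comparison will be biased, or in which direction. The gap is worth closing because remission is named as primary in the abstract and is part of the primary hypothesis.

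**What to change.** State that the GEE comparisons of remission and reliable change are run on multiply imputed data and pooled. Impute by dosage arm, using all BDI-II assessments, the randomization stratum (baseline BDI-II severity) and therapy type. Extend the imputation planned for the economic evaluation to the MINI-plus and SCID outcomes, which it does not yet cover. Report available-case GEE as a sensitivity analysis.

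The cost is modest: imputation models for binary diagnoses at two time points have to be added, but no new data are needed. Imputation still assumes that missingness depends only on observed data, so it does not protect against dropout driven by unrecorded change.
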